## Abstract

**Background:**

Although the detrimental effects of conventional combustible cigarettes on oral health and dental esthetics are well known, there is limited information about the long-term impact of combustion-free nicotine alternatives (C-F NA) such as e-cigarettes or heated tobacco products.

**Objective:**

This multicenter, prospective, 3-parallel-arm randomized controlled trial will investigate whether switching from combustible cigarettes to C-F NA will lead to measurable improvements in oral health parameters and dental esthetics over 18 months in adult smokers with limited gum disease.

**Methods:**

Regular smokers not intending to quit and without clinical signs of periodontitis will be randomly assigned (1:4 ratio) to either standard of care with brief cessation advice (control group; arm A) or C-F NA use (intervention group; arm B). The study will also include a reference group of never smokers (reference group; arm C). The primary end point is the change in the Modified Gingival Index (MGI) score from baseline between the control arm (arm A) and the intervention arm (arm B) at the 18-month follow-up. In addition, the study will analyze the within- and between-group (arms A, B, and C) changes in MGI assessment, plaque imaging, dental shade quantitation, tooth stain scores, and oral health–related quality of life questionnaires measured at each study time point. All participants will attend a total of 7 clinic visits: screening, enrollment, and randomization (visit 0); baseline visit—day 14 (visit 1); day 90 (visit 2); day 180 (visit 3); day 360 (visit 4); and day 540 (visit 5). This multicenter study will be conducted in 4 dental clinics in 4 countries. The statistical analysis will involve descriptive statistics for continuous and categorical data. Primary end points will undergo tests for normality and, based on distribution, either a 2-sided *t* test or Mann-Whitney *U* test. Linear mixed model with random factors center and study arms by center will also be applied. Secondary end points, including MGI assessment and quality of life, will be subjected to similar tests and comparisons. Only if one value of the parameter MGI is missing after day 1, the last available observation will be carried forward. The analysis will be performed on the substituted data. Secondary parameters will not have missing value replacement.

**Results:**

Participant recruitment began in October 2021, and enrollment was completed in June 2023. Results will be reported in 2025.

**Conclusions:**

This will be the first study to provide key insights into oral health benefits or risks associated with using C-F NA in smokers who are seeking alternatives to cigarette smoking.

**Trial Registration:**

ClinicalTrials.gov NCT04649645; https://clinicaltrials.gov/ct2/show/NCT04649645

**International Registered Report Identifier (IRRID):**

DERR1-10.2196/53222

## Introduction

### Background

Periodontal diseases, commonly including gingivitis and periodontitis, arise in response to the accumulation of oral bacteria in the gingival sulcus and are characterized by tissue changes in the periodontium that occur as part of the inflammatory process [1]. Gingivitis is characterized by inflammation such as redness, swelling, or bleeding on gentle provocation of the gingival sulcus, whereas periodontitis exhibits increased probing depth, clinical attachment loss, and radiographic alveolar bone loss, reflecting the destructive aspects of the disease process [2,3].

Periodontal disease is a well-known independent risk factor for cardiovascular disease [4,5], and reducing gingivitis and periodontitis is likely to have an overall positive impact on human health in general.

There are multiple risk factors for periodontal disease, and cigarette smoking is considered among the key independent risk factors for the development and progression of periodontal disease [6-9]. Depending on the disease definition and extent of exposure to cigarette smoke, the risk of developing destructive periodontal disease is 5- to 20-fold higher in smokers than in nonsmokers [10]. Cigarette smokers appear to be prone to more severe periodontal manifestations even after adjusting for age, education level, history of diabetes, BMI, alcohol consumption, perceived mental stress, and oral hygiene levels [11]. In addition to periodontal diseases, cigarette smoking can cause visible dental manifestations, including dental discoloration and tobacco stains, the intensity of which mainly depends on smoking duration and frequency [12]. In a large cross-sectional study in the United Kingdom [13], smokers were more likely to report dental discoloration and being dissatisfied with their own tooth color compared with nonsmokers. Dissatisfaction with teeth appearance (because of enamel discoloration and tobacco stains) is often perceived as a significant social problem for smokers [14,15].

The importance of dental care and oral health for healthy longevity is emphasized in the 2022 declaration of the World Health Organization (WHO) for which greater advocacy is needed to increase the prominence of oral health on the global health agenda. Moreover, reducing oral health issues calls for stronger policies addressing the determinants of oral diseases and no communicable diseases and to tackle inequalities through inclusive universal health care access [16]. More recently, the WHO has provided policy recommendations for integrating brief tobacco interventions into oral health programs in primary care in accordance with the WHO Oral Health Program and as part of the WHO Global action plan on the prevention and control of noncommunicable diseases, particularly pertaining to the needs of low- and middle-income countries [17].

Although it is clear that abstaining from smoking will have beneficial effects on oral health and overall dental esthetic, most smokers are reluctant to seek formal treatment to stop smoking, with the vast majority making attempts to quit without assistance [18,19]. Consequently, novel and efficient approaches are required.

Although not authorized as medications for smoking cessation, combustion-free technologies for nicotine delivery, such as e-cigarettes (ECs) and heated tobacco products (HTPs), have become de facto harm reduction tools from cigarette smoke [20,21] and aid in quitting smoking [22,23].

Combustion-free technologies for nicotine delivery such as ECs and HTPs offer substantial reduction in exposure and harm to harmful constituents compared with tobacco cigarettes [24-27], but there is limited information about the long-term impact on oral health and dental esthetics in people who use combustion-free nicotine alternatives (C-F NA).

### Objectives

This multicenter, prospective, randomized, controlled, 3–parallel arm trial will be the first to determine whether adult smokers who switch to C-F NA will experience measurable improvements in oral health parameters and dental esthetics. A group of never smokers will also be recruited for comparative measures of the study parameters.

Data from this study will provide valuable insights into the overall potential of C-F NA in reducing the risk of periodontal diseases and consequential cardiovascular risk. In addition, the findings may have important implications for reducing the smoking burden globally, especially for smokers for whom bad breath or poor dental esthetic is a significant concern. For these individuals, an oral-centric narrative (such as achieving a healthier and brighter smile) may serve as a more compelling reason to quit smoking than the fear of future lung cancer or cardiopulmonary diseases.

## Methods

This is a multicenter, 3-parallel-arm, randomized controlled trial of 18 months duration designed to assess whether cigarette smokers switching to C-F NA will undergo measurable improvements in oral health parameters and dental esthetics as a consequence of avoiding exposure to cigarette smoke. This study aims to assess differences in study end points of oral health parameters and dental esthetics at multiple study time points between smokers switching to C-F NA and smokers who continue to smoke.

### Study Population

Eligible participants will be healthy adult regular cigarette smokers (self-reported daily smoking of >10 cigarettes per day for at least 5 consecutive years) and never smokers without clinical signs of periodontitis.

Smokers will be offered access to free smoking cessation programs. Only those who refuse to participate in the smoking cessation program and express willingness to switch to C-F NA will be eligible for randomization.

Never smokers (those who have smoked <100 tobacco cigarettes in their lifetime) will also be included as a reference group.

Participants will be required to satisfy all the inclusion criteria as presented in Textbox 1.

Inclusion and exclusion criteria.
**Inclusion criteria for smokers (study arms A and B)**
Adults (aged 18-50 years)Cigarette smokers of ≥10 cigarettes per daySmoked for at least 5 consecutive years before screeningVerified smoking status by exhaled breath carbon monoxide (CO) ≥7 ppm at screeningWillingness to switch to a combustion-free nicotine alternatives, if required by the randomizationRefusal to participate in smoking cessation programsPresence of at least 10 natural anterior teeth in total (cuspid to cuspid and lower and upper jaw)Healthy participants, not taking regular medications for chronic medical conditionsAccepting to comply with the requirements of the study, including installing an app on their smartphone
**Inclusion criteria for never smokers (study arm C)**
Adults (aged 18-50 years)Have not smoked >100 tobacco cigarettes in their lifetimeVerified nonsmoking status by exhaled breath CO <7 ppm at screeningPresence of at least 10 natural anterior teeth in total (cuspid to cuspid and lower and upper jaw)Healthy participants, not taking regular medications for chronic medical conditionsAccepting to comply with the requirements of the study, including installing an app on their smartphone
**Exclusion criteria for smokers (study arms A and B) and never smokers (study arm C)**
Significant oral soft tissue pathology or any type of gingival overgrowth other than plaque-induced gingivitisPeriodontitis based on the 2017 World Workshop on the Classification of Periodontal and Peri-Implant Diseases and Conditions [28], which requires the following:Detectable interdental clinical attachment loss ≥3 mm at ≥2 nonadjacent teethBuccal or oral clinical attachment loss ≥3 mm with pocketing ≥3 mm detectable at ≥2 teethOnly participants with mild to moderate gingivitis will be recruitedFixed and removable orthodontic appliances or removable denturesAny other medical condition that, in the opinion of the principal investigator, would jeopardize the participant’s safety or diminish the validity of the study resultsA course of treatment with any medications thatinterfere with the cyclooxygenase pathway (eg, anti-inflammatory drugs including aspirin and ibuprofen) within 3 days before each visitare known to have antibacterial activity (eg, antibiotics) within 7 days before each visitSignificant history of alcohol or drug abuse within 24 months before screening, as determined by the investigatorFor smokers, planning to quit smoking within the next 6 monthsFor smokers, regular use of nicotine (eg, e-cigarettes, nicotine replacement therapy, nicotine pouches) or tobacco products (eg, heated tobacco products, oral smokeless) other than their cigarettes within 14 days of screeningPregnant or breastfeeding or intention to become pregnant during the studyActive participation in another clinical trial

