**Figure 2 figure2:**
[figure not shown]
Study flow diagram of study participants. C-F NA: combustion-free nicotine alternatives.

Screening visits will be performed within 28 days before enrollment to verify the eligibility criteria (visit 0; Figure 2). During the screening visit, sociodemographic data, medical and oral health history, detailed information about nicotine and tobacco consumption, and interest in trying C-F NA will be recorded. Screening for periodontal disease will be performed to exclude periodontitis, as per the definition of the guidelines of the 2017 Classification of Periodontal and Peri-implant Diseases and Conditions [28]. Smokers will be offered a smoking cessation program as per local guidelines. Any smokers who express the intention of booking for the cessation program or to quit smoking in the next 6 months will be urged to do so and will not be recruited in the study. Participants taking part in the study will be informed that they are free to quit smoking and withdraw from the study at any time. Moreover, smokers will be encouraged to quit smoking at every contact throughout the study.

Within 28 days of the screening visit, eligible participants will be invited to attend an enrollment visit (visit 0). Inclusion and exclusion criteria will be verified again. Smokers will be reminded of the risks associated with smoking before enrollment in the study and that they are free to voluntarily quit smoking and nicotine or withdraw from the study at any time. All participants will undergo a series of measurements (Tables 1-3) followed by dental scaling and polishing procedures to remove calculus, plaque, and stain.

Smokers not intending to quit will then be randomly assigned to either the control (arm A) or the intervention (arm B) group. The randomization sequence will be generated by a computer, with an allocation ratio of 1:4 (arm A: arm B) to accommodate for the estimated 25% proportion of participants achieving a sustained reduction in cigarette consumption of at least 90% in arm B (as detailed in the Statistical Considerations section). Smokers in the control group (arm A) will receive standard care, inclusive of cessation counseling (ie, VBA) at each study visit. Smokers in the intervention group (arm B) will have the option to try and choose a preferred C-F NA (ECs and HTPs) from a given pool of popular options present in the respective markets and will also receive VBA.

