Individuals who have never smoked will be allocated to the reference group (arm C). Never smokers in the reference group will serve as comparators for assessing any background changes in the primary study end point (ie, Modified Gingival Index [MGI]) that may occur over time. Although never smokers will not undergo randomization, efforts will be made to achieve a comparable distribution of sex and age across all study arms.

The trial is designed as an unblinded trial because of the nature of the intervention, where participants and trial staff cannot be blinded to the specific intervention being provided. However, data analyses will be conducted blind to study arms allocation. All other trial staff who have access to outcome data will remain blinded until prespecified data analyses will be completed.

Baseline measurements will be performed at visit 1 (baseline visit) and 14 days after scaling and polishing procedures at enrollment (visit 0). Study measurements will include MGI assessment, plaque imaging, dental shade quantitation, tooth stain scores, and oral health–related quality of life questionnaires (Tables 1-3).

Smokers in arm B will be provided with a C-F NA of their choice. They will receive training and counseling on how to use the chosen C-F NA and will be provided with a full 2-week supply of the required consumables (cartridges or pods or e-liquid refill bottles for ECs and tobacco sticks for HTPs). Participants wishing to use an HTP will receive one kit and a supply of tobacco sticks of their choice. They will receive the number of tobacco sticks per day corresponding to the number of cigarettes smoked per day at baseline. Participants wishing to use a vaping product will receive one vaping kit and a supply of e-liquids of their choice. Products will be supplied at each subsequent visit throughout the study according to the study product supply schedule in Table 4.

After the baseline visit, participants will be invited to attend 4 more clinical visits (visits 2-5) to repeat study measurements (Tables 1-3).

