Fifth, personal oral hygiene and dietary patterns can significantly influence both primary and secondary study end points. To mitigate this impact, a standardized approach to oral hygiene will be implemented within the study parameters. Participants will be explicitly advised against altering their established oral hygiene practices for the duration of the study. Furthermore, adherence to specific restriction criteria before each scheduled study visit will be emphasized, aiming to prevent any confounding of the collected data. Recognizing the variable effects stemming from individual oral hygiene and dietary habits, we incorporated a cohort of never smokers as a reference group. This inclusion serves to establish a benchmark for comparison and analysis. To address the inherent challenge of ensuring consistent measurement of study end points, especially in cases involving diverse operators across multiple sites, we will provide comprehensive training and implement meticulous calibration procedures.

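### The exclusion for other nicotine and tobacco products covers smokers only, so regular users of such products are eligible for the never-smoker reference arm

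*Protocol article*

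**What the plan says.** The exclusion list in Textbox 1 covers all three arms (its heading runs "Exclusion criteria for smokers (study arms A and B) and never smokers (study arm C"). One of its items excludes, for "smokers, regular use of nicotine (eg, e-cigarettes, nicotine replacement therapy, nicotine pouches) or tobacco products (eg, heated tobacco products, oral smokeless) other than their" cigarettes, with a window of 14 days before screening. By its opening words it applies to smokers only.

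Arm C is defined by cigarettes. The Study Population section states: "Never smokers (those who have smoked <100 tobacco cigarettes in their lifetime) will also be included as a reference group". The inclusion criteria for arm C require that participants have "not smoked >100 tobacco cigarettes in their" lifetime and that exhaled CO is below 7 ppm at screening.

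The protocol gives this arm a clear task. Under Study Design, "Never smokers in the reference group will serve as comparators for assessing any background changes in the primary study end point". The Discussion, explaining why never smokers were included, says: "This inclusion serves to establish a benchmark for comparison and analysis". The Abstract adds that "the study will analyze the within- and between-group (arms A, B, and C) changes" in MGI, plaque, shade, stain and quality of life.

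**The concern.** Arm C is meant to show what happens to gums and teeth without the exposures under study. The protocol treats regular use of e-cigarettes, heated tobacco, pouches or smokeless tobacco as a reason to keep a smoker out of arms A and B. It does not apply that rule to the group meant to be unexposed. A regular user of the products tested in arm B could therefore be counted in the benchmark against which arm B is read. At stake is the meaning of the comparisons with arm C, and of any description of that arm as free of nicotine and tobacco.

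**Working it through.** **Reading the criteria.** Take a never smoker who vapes daily, has smoked fewer than 100 cigarettes and has exhaled CO below 7 ppm.

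- Lifetime cigarettes: passes. No other product is named.
- Exhaled CO: the protocol uses it to verify smoking status and calls the products at issue combustion-free. It offers no nicotine-specific test, and pouches and oral tobacco produce no smoke.
- Nicotine and tobacco product item: does not apply, because it is limited to smokers.
- Remaining exclusions: oral pathology, periodontitis, appliances, other medical conditions, medication, alcohol or drug abuse, pregnancy and other trials. None clearly bars this person.

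The person is eligible for arm C as the criteria are written.

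**Whether the planned analysis closes the gap** (Statistical Analyses section). The regression lists use of combustion-free products among the possible predictors. The between-group analysis of covariance adjusts only for age, gender and oral hygiene frequency. The *t* and Mann-Whitney comparisons are unadjusted. The gap therefore stays open in the comparisons of arm C with A and B.

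**The plan's own figure.** The arm C size of 40 was set empirically, so there is no formula to reproduce. The 77 per group for A versus B does reproduce. With a difference of 0.10, SD 0.21, one-sided 5% and the noncentral *t*, power is 0.8993 at 76 and 0.9026 at 77. The point here does not depend on that figure.

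**Size.** The inputs are:

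- n = 40 (Sample Size Calculation).
- SD 0.21, taken from the A-versus-B calculation and assumed to hold in arm C.
- An effect d = 0.10 of product use on MGI change. This is an assumption that borrows the planned A-versus-B difference.
- A share f of users. This is an assumption, as the protocol gives none.

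Each user is 1/40 = 2.5% of the arm. The shift in the arm C mean is f × d. The standard error of that mean is 0.21/√40 = 0.033, with a 95% half-width of 1.96 × 0.0332 = 0.065. The chance of at least one user is 1 − (1 − f)^40.

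| Assumed share f | Expected users | Chance of at least one | Shift (d = 0.10) | Shift / standard error |
|---|---|---|---|---|
| 2% | 0.8 | 55% | 0.002 | 0.06 |
| 5% | 2 | 87% | 0.005 | 0.15 |
| 10% | 4 | 98.5% | 0.010 | 0.30 |
| 20% | 8 | >99.9% | 0.020 | 0.60 |

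Even a small share makes at least one such participant likely, but the shift in mean MGI change stays below the standard error across this range.

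**The case against.** Much of the case on the other side is sound.

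- **The primary result is not touched.** It compares arms A and B. Arm C is not randomized and has no formal sample size. This stands.
- **The effect and the number of users are both assumed.** The 0.10 comes from the contrast between continued smoking and switching, and is not an effect of these products in people who never smoked. The resulting shifts lie within sampling noise. This stands for MGI; for stain and shade the protocol gives nothing from which to compute a shift.
- **The direction of bias is not established.** A reader might infer that switchers will be made to look closer to never smokers than they are. That holds only if the products themselves affect the outcomes, which the protocol treats as an open question. Arm B is not a pure product group either: the sample size section expects only about 25% to abstain or cut smoking by at least 90%.
- **Use may well be recorded.** A reader might infer from Table 3, which has no row for product use, that use in arm C goes unseen. The documents do not support this. Table 1 for arm A has no such row either. Screening records "detailed information about nicotine and tobacco consumption", the Study Design text describes app and diary monitoring of product use, and Table 3 installs the app in arm C.
- **The regression includes product use as a predictor.** True, but it does not carry over to the between-group comparisons.

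One further defence is that handling of this kind belongs in the statistical analysis plan. That is fair for the analysis, but the eligibility rule is stated in this document, and its wording admits these participants.

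**Conclusion.** The gap is real and lies in the stated wording: regular users of combustion-free or oral nicotine products are eligible for the never-smoker reference. The consequence is confined to the arm C benchmark and the secondary comparisons with arm C. If the products affect the outcomes, users in arm C would move the reference towards arm B. If they do not, nothing moves.

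The size is unknown. With 4 to 8 users of 40 and an assumed effect of 0.10, the mean MGI change in arm C shifts by 0.01 to 0.02, about 0.3 to 0.6 standard errors at an assumed SD of 0.21. The protocol does not say that any such participant was enrolled, and a count of zero would settle the matter.

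**What to change.** Extend the product item to arm C in the wording, either by removing its restriction to smokers or by adding a matching criterion. Enrollment closed in June 2023, so this alone does not change who entered.

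For the data in hand:

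1. Use the nicotine and tobacco history from screening, together with app or diary data, to count arm C participants with regular use. Apply the 14-day screening window already set for smokers.
2. Before the data are analysed, prespecify the arm C comparisons with and without these participants.
3. Describe the reference as free of nicotine and tobacco product use only for the set without them.

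The cost is a change of wording and a filter on data the protocol says are collected. The downside is that arm C may lose a few of its 40 participants in that set. Under the same SD of 0.21, losing 4 raises the standard error from 0.033 to 0.21/√36 = 0.035, and losing 8 raises it to 0.21/√32 = 0.037.
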